#### Awareness creation and community mobilization in the intervention arm

Recruitment will be done via media advertisements, posters, billboards, and community awareness programs targeting all eligible women (women between 40–70 years) to participate in screening at designated PHCs.

Radio jingles in English and Yoruba, the local language in the study area, will be aired on the three major radio stations that cover the LGAs. This will be done twice daily for two weeks before the launch of the program and weekly subsequently, spanning the entire period of the study. A fifteen-minute twice-weekly local television program will also be broadcasted for two weeks before the commencement of the program. The aim of this is to sensitize people to the nature of the disease, remedy inaccurate notions about the disease, and highlight the benefits of screening. This will be followed by short weekly television advertorials updating people about the program and inviting women who are yet to be screened.

Awareness programs in the form of town hall meetings will be held quarterly in various districts across the LGAs. This will feature talks by breast cancer survivors, key opinion leaders in the LGA, and medical personnel. The awareness programs will utilize the health belief model constructs, which address the various issues associated with behaviour change.

Handbills and educational materials detailing the nature of the program, as well as educational materials about breast cancer and instructional details on breast examination will be distributed to women at strategic locations, such as markets and places of worship.

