#### Screening and diagnostic evaluation schedule in the intervention arm

In the intervention arm, consecutive consenting asymptomatic (40–70 years) and symptomatic (30–70 years) women will undergo screening and diagnostic evaluations respectively. Asymptomatic women (age 40–70 years) presenting for screening at designated PHCs will be evaluated by trained CHNs. Evaluation will entail a focused breast history, CBE, and iBE. Women with positive findings on CBE or iBE will be scheduled for another visit to have breast imaging and if indicated a breast biopsy. Women with negative findings on CBE and iBE will be scheduled for a similar repeat annual evaluation. Women will, however, be told to return at any time if any abnormality is noticed before their scheduled visit. Every woman who is screened will be given a breast health card (pink card) containing her name, contact information, a summary of findings on evaluation, and the date of the next examination. A duplicate copy of the breast card will be kept at the health centre for reference and follow-up. In addition to the breast health card, a detailed record of CBE and iBE findings for each patient will be kept by the PHC Nurse.

Symptomatic women (age 30–70 years) without an obvious lesion will be evaluated like the asymptomatic population, with focused breast history, CBE, and iBE. Those with positive findings will progress to imaging while those with negative findings will be scheduled for repeat evaluation on a short-term basis (one month). If symptoms persist at the time of the next evaluation, they will progress to imaging regardless of CBE and iBE findings.

Symptomatic women (age 30–70 years) with obvious breast lesion(s) will undergo focused breast history and CBE examination and will be scheduled to have imaging evaluation and breast biopsy if indicated (Fig 3).

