Participation rate: This will be determined by calculating the percentage of women screened/evaluated of the total number of eligible women based on census data. A participation rate of 70% will be considered satisfactory in the intervention arm. The number of screened/evaluated women in the intervention and control arms will also be compared.Cancer detection rate (CDR): This refers to the number of histopathologically diagnosed cases of breast cancer per 1,000 evaluated populations in both screening and diagnostic groups. This will be compared between the control and intervention arms.Timeline from presentation to treatment: The time interval between presentation for breast evaluation and treatment in OAUTHC of the cases in the two arms will be compared.Retention rate: The retention rate refers to the number of women who return for repeat annual screening of the total initial number of women initially screened in the first year. A repeat screening within a year and a half will be considered acceptable for this two-year study. To ensure all accrued participants get their second screen, we will follow them up beyond the initial study period as needed.Abnormal call rate: This is defined as the number of women with abnormalities detected on iBE and/or CBE requiring further evaluation either by imaging with or without biopsy out of the total number of asymptomatic and symptomatic without an obvious lesion participating in the study. There are 2 groups of participants (diagnostic and screening) in each of the 2 arms (intervention and control). The screening group constitutes the asymptomatic participants while the diagnostic group constitutes the symptomatic participants. The interventions in this study include enhanced CBE (CBE + iBE), community-based diagnostic evaluation (with portable ultrasound and mobile mammography), and biopsy (if warranted). To evaluate which of CBE and enhanced CBE was of greatest value, another layer of analysis will be provided to address this question by comparing the concordance of the two with imaging which is the gold standard. This study also provides an additional opportunity to evaluate the iBE device.

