### Statistical analyses

All data entered into the REDCap database will be exported as a dataset into R 4.2. Sociodemographic characteristics of the participants will be assessed using medians and interquartile ranges (IQR) for continuous variables and counts and percentages for categorical variables. Participation rate, retention rate, abnormal call rate, rate of late-stage diagnosis, and CDR will be reported as proportions with 95% exact confidence intervals. As for late-stage diagnosis, stage 4 cancers will be considered late-stage. The above-mentioned metrics will be compared between the intervention and control arms using Chi-square tests or Fisher’s exact test. The time intervals from presentation to treatment will be reported using medians and IQR and will be compared between the intervention and control arms using the Wilcoxon rank-sum test. The rate of late-stage diagnosis will be estimated and compared between the intervention and control arms on a yearly basis, starting from baseline, to assess if the intervention arm shows betterment in this rate consistently. Bonferroni correction for type I error will be implemented (α* = 0.0167) for this comparison. A logistic regression analysis which accounts for the ward (random effect) in which the patient was examined will also be performed with late-stage diagnosis as the dependent variable and time of screening, the interaction between the allocated groups (intervention and control arms), and time of screening as the independent variables. For all statistical comparisons (other than the one mentioned immediately above), the type I error rate (α) will be set to 0.05. All statistical analyses will be conducted using R 4.2 software [24]. Sample size calculations were done using the clinfun package of the R 4.2 software [25].

We do not anticipate any missing data due to loss of follow-up because the research team will make every effort to retain recruited participants. However, if missing data issues do arise, we will implement multiple imputation techniques, which impute missing data under the missing at random (MAR) assumption. Sensitivity analysis of the findings after multiple imputations will thereby be performed and these findings will be compared to those obtained from complete case analyses.

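### The abnormal call rate is put into a between-arm test, although the iBE/CBE finding that defines it is described only for the intervention PHCs

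*Protocol article*

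**What the plan says.** The secondary outcomes under Program evaluation and outcome measures define a single abnormal call rate. Its numerator is women whose iBE and/or CBE abnormality needs imaging, with or without biopsy. Its denominator is "out of the total number of asymptomatic and symptomatic without an obvious lesion participating in the study". The same text describes two groups of participants and says that both occur in each arm: "The screening group constitutes the asymptomatic participants while the diagnostic group constitutes the symptomatic participants".

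That outcome list announces an arm comparison for participation (number evaluated), CDR and time to treatment, but none for the call rate. The comparison comes from the Statistical analyses section: "Participation rate, retention rate, abnormal call rate, rate of late-stage diagnosis, and CDR will be reported as proportions with 95% exact confidence intervals", followed by "The above-mentioned metrics will be compared between the intervention and control arms using Chi-square tests", with Fisher's exact test as the alternative. The type I error rate is 0.05.

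The two arms are described differently:

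- **Intervention arm.** Recruitment is by publicity "targeting all eligible women (women between 40–70 years) to participate in screening at designated PHCs". Nine nurses, three in each of three PHCs, are trained in CBE and iBE (Sample size of community health nurses; Training staff in the intervention arm).
- **Control arm.** Women are not invited to screening and are expected to come to the PHC when they have a breast complaint. A nurse reviews them and decides whether to refer (Control arm). Before the study, PHC nurses had no core experience of breast cancer screening (Training staff in the intervention arm).

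**The concern.** A test of two proportions is informative only if both are the same quantity, measured in the same way on comparable women. Here the event is a finding on a particular examination. That examination is described for the intervention PHCs and not for the control PHCs, so what would count as a call in a control PHC is undefined. The only available substitute is a nurse's decision to refer, which is a different event.

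The denominators are also likely to differ in composition. One arm actively brings in asymptomatic women, while the other mostly waits for women with symptoms. If symptomatic women are called more often, the pooled rates will differ even where the group-specific rates are equal.

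The protocol presents its outcomes as metrics of programme impact, so a small p value here would invite that reading.

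**Working it through.** **1. Is the rate in the tested list?** Yes. It is named in the sentence on proportions, and the comparison sentence applies to the metrics listed above it without exception.

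**2. Is the numerator available in both arms?**

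| Element | Intervention PHCs | Control PHCs |
|---|---|---|
| Who attends | Asymptomatic women invited (40–70 years); symptomatic women (30–70 years) | Not invited; expected with complaints |
| Examination | Focused history, CBE and iBE by trained nurses (CBE without iBE for obvious lesions) | Nurse review; no iBE or trained CBE described |
| Route to imaging | Positive CBE or iBE | Nurse's judgement, or self-referral to OAUTHC |

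The protocol gives no iBE/CBE reading for a control PHC attender.

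**3. How far could case mix alone move the result?** The protocol gives no call rate and no symptomatic share, so everything in this step is assumed except the projected numbers of women: 1,582 intervention and 164 control (Sample size of cases). Those numbers include women with an obvious lesion, whom the call rate excludes, so they are somewhat too large.

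Let a be the call rate in asymptomatic women, b the rate in symptomatic women without an obvious lesion (both equal across arms), and s the symptomatic share:

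- pooled rate = (1 − s)·a + s·b
- arm difference = (difference in s) × (b − a)

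With a of 2–10% and b of 20–60%, b − a runs from 20 − 10 = 10 points to 60 − 2 = 58 points. A 10-point gap in symptomatic share then moves the pooled rate by 1.0–5.8 points, a 20-point gap by 2.0–11.6, and a 40-point gap by 4.0–23.2.

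The chance of a significant result (normal approximation, two-sided 0.05) is Φ((d − 1.96·SE₀)/SE₁), where d is the arm difference, SE₀ uses the pooled proportion and SE₁ the separate proportions. Worked for a = 5%, b = 30% and shares of 30% v 70%:

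- intervention: 0.7 × 5% + 0.3 × 30% = 12.5%
- control: 0.3 × 5% + 0.7 × 30% = 22.5%
- pooled proportion: (1,582 × 0.125 + 164 × 0.225)/1,746 = 0.134
- SE₀ = 0.0280 and SE₁ = 0.0337, so (0.100 − 0.0548)/0.0337 = 1.34, and Φ(1.34) is about 91%

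| Symptomatic share (intervention v control) | a = 5%, b = 30%: pooled rates | Chance of p < 0.05 | a = 10%, b = 20%: pooled rates | Chance of p < 0.05 |
|---|---|---|---|---|
| 30% v 70% | 12.5% v 22.5% | 91% | 13.0% v 17.0% | 31% |
| 30% v 50% | 12.5% v 17.5% | 45% | 13.0% v 15.0% | 12% |
| 50% v 60% | 17.5% v 20.0% | 13% | 15.0% v 16.0% | 6% |

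With equal shares the chance is the nominal 5%. In every row the group-specific rates are identical in the two arms. Any effect of the different examination comes in addition, and its size is unknown.

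**The case against.** The strongest reply is that the protocol never singles this rate out for testing. The outcome list announces no arm comparison for it, the 1.5-year look at it is descriptive, and Fig 4, which is not shown, may assign outcomes to arms. On that view the comparison is a loose sentence in a condensed article. This supports calling the point minor. It does not remove it, because the tested list names the rate and the descriptive label covers only the 1.5-year look.

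Second, the protocol says both arms contain screening and diagnostic groups, and it promises control women the same work-up at OAUTHC. So the control arm should not be treated as wholly symptomatic, and extreme contrasts of symptomatic share are not fair scenarios. But having both groups in each arm does not make their shares equal. The shared work-up begins only once a woman reaches the hospital, by self-referral or after nurse triage, and the protocol does not say that iBE is used there.

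Third, CBE plus iBE is part of the intervention, so a difference due to the examination is partly the programme itself. That is correct. The complaint is therefore the narrower one that the control PHC numerator is not an iBE/CBE finding.

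A reader might infer more than the protocol supports:

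- **Pooling as such is wrong.** It is not. A programme-level call rate in a mixed service is a legitimate descriptive figure.
- **The different recall schedules distort the rate.** Negative asymptomatic women return after a year and negative symptomatic women after a month, but nothing shows that this interval changes a rate that counts women.
- **The rate fails as a measure of imaging demand.** The protocol does say "If symptoms persist at the time of the next evaluation, they will progress to imaging regardless of CBE and iBE findings", but it never offers the call rate as total imaging demand.
- **First-year cancer yields prove the case-mix gap.** The yields were 13/791 = 1.6% and 12/82 = 14.6%. They fit a difference in case mix, but they count obvious-lesion women whom this rate excludes, so they are only indirect.

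**Conclusion.** The point holds in a limited form. As written, the abnormal call rate enters an unadjusted between-arm test although its defining event is not described for the control PHCs and the symptomatic share is likely to differ. A significant difference could not be read as a programme effect.

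The size is not computable from the document. Under the assumed rates and shares shown, the chance of a significant result with no difference in group-specific rates runs from barely above nominal (6%) to 91%. The direction of the case-mix part assumes that symptomatic women are called more often.

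This is a minor matter: a secondary outcome with no decision threshold. The primary comparison of stage at diagnosis does not depend on it.

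**What to change.** **Statistical analyses:** take the abnormal call rate out of the metrics tested between arms. Report it for the intervention arm with exact 95% intervals, separately for asymptomatic women and for symptomatic women without an obvious lesion. A pooled programme figure may stand alongside.

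**Program evaluation and outcome measures:** state the same reporting in the definition, and use the same rows in the 1.5-year descriptive analysis. Any control-arm referral rate should be descriptive, by group, and labelled as usual nurse review rather than as an iBE/CBE call.

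**Cost:** a few words and an extra table row. The CRF already holds CBE and iBE findings, and the two groups are already named. One p value is given up, and within-group intervals are wider. At assumed rates of 5% and 40% and a symptomatic share of 10–50%, the exact 95% interval widths in percentage points are:

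| Intervention women | Asymptomatic | Symptomatic | Pooled |
|---|---|---|---|
| 1,582 (two-year projection) | 2.3–3.2 | 6.9–15.8 | 2.8–4.2 |
| 791 (first year) | 3.4–4.6 | 9.9–22.5 | 4.0–5.9 |

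For example, 63/158 symptomatic women gives 32.2–48.0% and 71/1,424 asymptomatic women gives 3.9–6.2%. Obvious-lesion women are not subtracted, because their number is not given.

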This underscores the need for a cost-effective screening model tailored to the available human and infrastructural capabilities and designed to meet individual patient needs.

Various guidelines, such as the Breast Health Initiative Resource Stratified guidelines, have been proposed for context-appropriate breast cancer screening in resource-limited settings [15]. This includes the role of primary health care workers in performing CBE, creating awareness, and patient navigation for prompt treatment. Drawing from experiences of countries that have successfully demonstrated the feasibility of breast cancer screening performed by community workers using less expensive modalities, such as CBE, it is logical to build on such models [16–18].

The iBreast Exam (iBE) (UE Life Sciences, Philadelphia, PA) is a 510(k) FDA-cleared device that utilizes sensors to electronically palpate the breast when pressed against the skin. It can be used with minimal training. It does not distinguish malignant versus benign findings but identifies women who should undergo additional evaluation for a possible abnormality. This could be particularly useful in low-resource settings with limited breast imaging available [19].

A previous study in our population has shown that the combination of the iBE device with CBE has higher sensitivity for detecting suspicious breast lesions when compared to CBE alone (92%, 95% CI 77–98 vs 83%, 95% CI 67–94 respectively) [19]. This research builds on our previous results and findings of a study utilizing iBE in India [20]. This study proposes an early detection model that combines iBE with CBE to reduce the subjectivity of CBE, as the basic breast cancer screening tools for eligible women in the community and breast imaging (mobile mammography and ultrasound) for selected women based on clinical history, CBE, and iBE findings. The components of the triple mobile assessment in this proposed project are nurse breast exams (with iBE and CBE), mobile portable ultrasound, and mobile mammography.

This manuscript aims to describe the protocol for screening women between 40 and 70 years and diagnostic evaluation of women aged 30–70 years with breast symptoms in the first comprehensive community-based breast cancer program that offers screening, and diagnostic evaluation and provides a referral pathway and patient navigation for breast cancer treatment in Nigeria.

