#### Evaluation of patients with positive findings in the intervention arm

Women with positive CBE or iBE findings will be scheduled for imaging, which will be conducted by the Radiologist and mammography Technologist from OAUTHC who will visit the LGA with mobile ultrasound machines and a mobile 2D digital mammography unit once a month. The 2D mobile digital mammography machine is a General Electric (GE) dedicated mammography computed radiography system secured from Lilly Women’s Health, a non-Governmental Organization in Lagos State, South-west Nigeria, which is being rented to us for the proposed two-year study period. The mobile ultrasound machines are four mHealth ultrasound tablets available in the breast unit of the Department of Radiology, OAUTHC which were utilized for a just-completed study funded under the R21 category of National Institute of Health (NIH) “Tablet-based mobile Health ultrasound for point-of-care breast cancer diagnosis in Nigeria (1R21CA239784-01)”.

Patients from all the PHCs will be seen at a central location in the LGA. Patients with suspicious findings on imaging will undergo an ultrasound-guided core needle breast biopsy on the same day. Biopsy specimens will be fixed in 10% neutral buffered formalin immediately and transported to OAUTHC the same day for processing and pathology interpretation.

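### Judging CBE against CBE + iBE by concordance with imaging cannot give absolute accuracy and exaggerates the gap, because screening women are imaged only if one of the two tests is positive

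*Protocol article*

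**What the plan says.** Under Program evaluation and outcome measures (secondary outcomes, abnormal call rate), the protocol article adds an analysis of which of CBE and enhanced CBE was of more value. The method is "comparing the concordance of the two with imaging which is the gold standard". The same paragraph defines enhanced CBE: "The interventions in this study include enhanced CBE (CBE + iBE), community-based diagnostic evaluation". It also fixes the groups: "The screening group constitutes the asymptomatic participants while the diagnostic group constitutes the symptomatic participants".

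Who is imaged is set in the section on the screening and diagnostic evaluation schedule. For asymptomatic women: "Women with positive findings on CBE or iBE will be scheduled for another visit to have breast imaging". For those negative on both tests: "Women with negative findings on CBE and iBE will be scheduled for a similar repeat annual evaluation". The section on evaluation of patients with positive findings repeats the rule: "Women with positive CBE or iBE findings will be scheduled for imaging, which will be conducted by the Radiologist". The Introduction likewise describes "breast imaging (mobile mammography and ultrasound) for selected women based on clinical history, CBE, and iBE findings".

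The schedule section adds two routes to imaging, both for symptomatic women:

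- Women without an obvious lesion who test negative are re-evaluated at one month and imaged if symptoms persist, whatever the two tests show.
- Symptomatic women "with obvious breast lesion(s) will undergo focused breast history and CBE examination" and then go to imaging. No iBE is listed for them.

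The article describes no imaging of a sample of test-negative women and no correction for partial verification.

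**The concern.** The tests being compared decide who receives the reference standard. Under an either-positive reading of enhanced CBE, an asymptomatic woman reaches imaging only by being enhanced-CBE positive. In the imaged screening group that test does not vary, so no measure of agreement that needs both positive and negative results can describe it. CBE alone does vary there: it gains agreement for every iBE-only positive with normal imaging and loses it for every iBE-only positive with a suspicious finding.

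At stake is how the device result is reported. A concordance table from imaged women would show enhanced CBE with zero specificity and zero kappa whatever its true performance, and a gap in agreement much wider than the one in the screened population. The article intends this comparison to evaluate the device and to guide future studies, so a reader could take those figures at face value.

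**Working it through.** The article states no figure for this analysis, so there is none to reproduce. The check is the logic, followed by an illustration.

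**Logic.** Let E be positive if CBE or iBE is positive, and let only E-positive women be imaged. In the imaged set:

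- Every woman with suspicious imaging is E-positive, so apparent sensitivity is 100%.
- Every woman with normal imaging is E-positive, so apparent specificity is 0%.
- Agreement of E = TP/(TP + FP) = PPV.
- Chance-expected agreement for kappa = 1 × PPV + 0 × (1 − PPV) = PPV, which equals the observed agreement, so kappa = 0.

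**Inputs for the illustration.**

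- N = 4,100 evaluated women (Sample size of study participants). For simplicity all are treated as having both tests and following the asymptomatic rule.
- Sensitivity 92% for CBE + iBE and 83% for CBE (Introduction).
- Assumed, not in the article: suspicious imaging in 5%; specificity 95% for CBE and 90% for enhanced CBE.

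**Counts.** Suspicious: 0.05 × 4,100 = 205. Normal: 3,895.

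- Enhanced CBE: TP = 0.92 × 205 = 188.6; FP = 0.10 × 3,895 = 389.5; imaged = 578.1.
- CBE: TP = 0.83 × 205 = 170.15; FP = 0.05 × 3,895 = 194.75.
- iBE-only positives: 188.6 − 170.15 = 18.45 true and 389.5 − 194.75 = 194.75 false.

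| | Enhanced CBE agrees | CBE agrees | Difference in counts |
|---|---|---|---|
| Imaged only (578.1) | 188.6 (0.33) | 170.15 + 194.75 = 364.9 (0.63) | −176.3 |
| All imaged (4,100) | 188.6 + 3,505.5 = 3,694.1 (0.90) | 170.15 + 3,700.25 = 3,870.4 (0.94) | −176.3 |

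The difference in counts is the same in both rows (18.45 − 194.75 = −176.3), because a woman negative on both tests counts identically for each. Only the denominator changes: the gap is 176.3/578.1 = 0.30 in the imaged set and 176.3/4,100 = 0.04 in all women.

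For CBE in the imaged set, sensitivity is 170.15/188.6 = 0.902 (that is, 83/92), a valid relative sensitivity. Its apparent specificity is 194.75/389.5 = 0.50, against the 0.95 put in.

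**Range.** With assumed suspicious imaging of 1%, 3.5% or 10% and specificities (CBE/enhanced) of 98/95%, 95/90% or 90/80%:

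- Enhanced CBE in the imaged set: agreement 0.04 to 0.67, kappa 0 in all nine scenarios.
- Enhanced CBE with all women imaged: agreement 0.80 to 0.95, kappa 0.07 to 0.75.
- Gap in agreement: 0.13 to 0.49 among imaged women, against 0.02 to 0.10 with all imaged.

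**What the imaged set does identify.** In the 5% illustration:

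- Relative true-positive rate: 188.6/170.15 = 1.11.
- Relative false-positive rate: 389.5/194.75 = 2.0.
- Extra women imaged per extra suspicious lesion: 213.2/18.45 = 11.6.

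The unknown denominators cancel from both ratios, so unimaged women are not needed.

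**Precision.** The article projects 26 intervention-arm cancers in two years. If enhanced CBE found all 26 and the 83:92 ratio applied to cancers (an assumption, since those figures concern suspicious lesions), CBE would find 26 × 83/92 = 23.5. That leaves about two or three extra cancers, before women with obvious lesions are excluded.

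**The case against.** The strongest reply is that the comparison is not biased in direction. A reader might infer that partial verification can reverse the ranking, that every accuracy figure from the imaged set is an artefact, or that the comparative question cannot be answered. The documents do not support any of these. Double-negative women cancel from the paired difference, all iBE-only positives are scheduled for imaging, and CBE's sensitivity among enhanced-positive women is a sound relative quantity. How to weigh an extra false positive against an extra true finding is a question of value, not of verification. This part of the reply stands in full.

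Other points stand in part:

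- The article does not name sensitivity, specificity or kappa, and concordance could mean PPV, which is estimable for both tests. But the word naturally suggests agreement, and agreement proportions are what the gate distorts.
- The either-positive rule is not written into the definition of enhanced CBE. The abnormal call definition and the imaging rule both point to it. If both-positive were meant, enhanced CBE would vary, but double-negative women would still be unverified.
- The unit of analysis is not stated. At breast level, a woman imaged for one side could contribute a test-negative breast, though only among women already selected by a positive test.
- The Introduction lists clinical history among the grounds for imaging, but the schedule gives asymptomatic women no route on history alone.
- Some test-negative symptomatic women are imaged. They are selected by persistent symptoms and belong to the diagnostic group, so they do not repair the screening comparison.
- The article also mentions exploring the difference in cancer detection rate between the two modalities, which is close to a relative true-positive rate. It does not withdraw the concordance analysis.
- The statistic could be settled in an analysis plan not shown here. The point is not an omission: the metric and the imaging rule stated in the article do not fit together.

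**Conclusion.** The concern holds in a limited form. With enhanced CBE read as either-positive, it is positive in every imaged screening woman. Its absolute sensitivity, specificity and kappa cannot be estimated, and its agreement with imaging is only its PPV. Agreement proportions in the imaged set are distorted and their gap is exaggerated: 0.33 versus 0.63 instead of 0.90 versus 0.94 in the 5% illustration, about seven times as wide (4,100/578.1 = 7.1). The size depends on the assumed prevalence and specificities. The forced values do not; they follow from the imaging rule and the either-positive reading.

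The sign of the paired difference is preserved, and relative measures are valid. This is an additional analysis under the secondary outcomes, and the primary comparison of stage at diagnosis is unaffected.

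**What to change.** In the secondary outcomes text and the analysis plan:

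1. Define enhanced CBE as positive when CBE or iBE is positive, and state the unit of analysis.
2. Replace concordance with these measures, in women who had both tests: paired relative true-positive rate and relative false-positive rate (enhanced CBE over CBE) with confidence intervals, PPV of each, and extra imaging and extra biopsies per extra cancer.
3. Use histology as the reference for cancer and imaging category as the reference for suspicious lesions.
4. Report the symptomatic group separately. Leave women with obvious lesions out of the paired comparison, since no iBE is listed for them.
5. State that absolute sensitivity and specificity are not estimable from this design.
6. State that both ratios are at least 1 by construction, because enhanced CBE contains CBE, and that precision will be low with about 26 projected intervention-arm cancers before women with obvious lesions are excluded.
7. Report later cancers in double-negative women descriptively as interval cancers. They are not a lower bound on missed cancers, because some will have arisen after the examination.

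The cost is wording. The case report form already holds CBE, iBE, imaging and pathology results, and cases are already tracked at the primary healthcare centres and the referral hospital. No imaging, staff or change to patient care is added. What is given up is absolute accuracy, which the design could not supply.
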